Current evidence is insufficient to establish clinical practice recommendations due to the small sample sizes, unclear treatment details and different measurements of the outcome variable. There is urgent need to perform a high-quality randomized controlled trial (RCT) that is adequately powered, using the optimum intervention and validated outcome measurements. Furthermore, few of the prior studies included outcome measures of changes in physiological markers, ADLs, and QOL. Growing evidence suggests that a hybrid combination of aerobic exercise and cognitive training may provide additional benefits in cognitive performance that go beyond the effects of a single type of training in animals [23], community-dwelling elderly [24, 25], and stroke survivors [26]. A systematic review of combining exercise and cognitive intervention in older adults suggests that exercise sessions delivered *before* the cognitive training session prepares the brain for the compensatory recruitment process in the subsequent cognitive training sessions [25]. Aerobic exercise before cognitive training may increase arousal level, facilitate neurogenesis and enhance memory consolidation, which may benefit the memory retrieval and cognitive task performance that follows [27, 28]. Aerobic exercise training combined with cognitive training might be a plausible intervention to augment cognitive function and intensify rehabilitation outcomes.

We are conducting a single-blind, adequately powered, high-quality RCT to test the hypothesis that a sequential combination of aerobic exercise and cognitive training will promote cognitive performance in stroke survivors with cognitive impairment. Specifically, we aim to determine the treatment effects of the hybrid training, compared with exercise or cognitive training alone, on: (1) cognitive function and (2) physiological markers, daily function, quality of life, physical function, and social participation.

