### Sample size

No published research to date has investigated the effects of combining aerobic exercise with cognitive training on cognitive functions in patients with stroke; therefore, the sample size calculation was based on the effects of a similar study conducted by Kim et al. [29]. The study investigated the effects of 4 weeks of cognitive, combined, motor dual-task training on cognitive and motor function in stroke survivors. The Stroop test, Timed Up and Go (TUG) test, 10-Meter Walk Test (10MWT), Figure-of-8 Walk Test (F8WT) and gait speed were used to measure cognitive and motor abilities and were evaluated three times (before and after training and at the 2-week follow up). The results showed that compared to the single-task training, the active control group, dual-task training improves cognitive and motor functions in stroke survivors, and these training benefits were maintained for 2 weeks.

A priori power analysis (G*Power software 3.1) was used to estimate the number of participants needed for this project. On the basis of Kim’s work [29], the estimated sample size requirement is 20 patients for each group in a three-group study design given the lowest effect size (*f* = 0.30), power of 0.80, and two-sided type I error of 0.05. Allowing for 20% attrition at the 6-month follow up, we plan to recruit 25 participants for each group, resulting in a sample size of 75 participants.

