### Inclusion and exclusion criteria

Participants eligible for the study must comply with all of the following criteria before randomization: (1) unilateral ischemic or hemorrhagic stroke occurring at least 6 months before enrolment; (2) age between 20 and 90 years [30]; (3) MMSE score ≥ 19; (4) Montreal Cognitive Assessment (MoCA) < 26; (5) self-reported or informant-reported memory or cognitive complaints or Clinical Dementia Rating Scale (CDR) score ≤ 0.5; (6) able to follow the study instruction; (7) adequate cardiopulmonary function to perform aerobic exercise; and (8) able to walk with or without assistive devices. Patients who have one or more of the following criteria will be excluded from the study: (1) unstable medical history (e.g., recent myocardial infarction) that might limit participation; (2) other neurologic disorders (e.g., Parkinson’s disease, amyotrophic lateral sclerosis, multiple sclerosis); and (3) current participation in another interventional trial.

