### Analyses

We will use the chi square (χ^2^) test and analysis of variance to analyze differences in baseline characteristics and baseline outcome measures among the groups. Mixed-factor repeated-measures analysis of variance will be used to determine the intervention effect in the three groups. The within-subject factor will be time (pretest, posttest, and follow up), and the between-subjects factor will be group (COG, AE, and SEQ). Tukey’s test will be performed if a group × time interaction or a main effect is observed. Statistical significance will be set at 0.05 for all comparisons. In addition to *p* values, *η*
^2^ will also be calculated to determine the group difference for each outcome measure. Data analysis will be performed using PASW Statistics 18.0 software (SPSS Inc., Chicago, IL, USA).

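### The rule for post hoc testing treats the time and group main effects as equal in standing to the group × time interaction when the aim is the intervention effect

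*Protocol article*

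**What the plan says.** The Analyses section states the purpose of the model: "Mixed-factor repeated-measures analysis of variance will be used to determine the intervention effect in the three groups". Time has three levels (pretest, post-test, follow-up) and group has three (COG, AE, SEQ). The decision rule is that Tukey's "test will be performed if a group × time interaction or a main effect is observed". It does not say which main effect is meant or which means Tukey's test then compares. The significance rule is "Statistical significance will be set at 0.05 for all comparisons". Eta-squared "will also be calculated to determine the group difference for each outcome measure".

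The Background defines the question as a comparison between arms: "we aim to determine the treatment effects of the hybrid training, compared with exercise or cognitive training alone". The Discussion confirms that there is no passive control group, and the Interventions section keeps conventional therapy going in every arm. Entry requires "Montreal Cognitive Assessment (MoCA) < 26", and the MoCA is also listed as a primary outcome.

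**The concern.** In a randomised trial with a pretest, the treatment effect is the difference between arms after randomisation. Of the three terms in this ANOVA, only the group × time interaction isolates differential change between arms.

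- **Time main effect.** It pools the arms and says nothing about SEQ against AE or COG. A shared rise can come from repeated testing, from the conventional therapy given to everyone or, for the MoCA, from selecting patients below a cut-off on the same scale. Without a passive control these cannot be told apart from training.
- **Group main effect.** It averages over all three visits. The pretest contributes no treatment effect, only chance imbalance.

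The rule gives all three terms the same standing under the label of intervention effect. At stake is which result the trial may call a treatment effect, and how well the analysis identifies the better arm.

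**Working it through.** **Inputs from the article.** Sample size section: "given the lowest effect size (*f* = 0.30), power of 0.80, and two-sided type I error of 0.05", with 20 patients per group and 20% attrition. The attrition step reproduces: 20 / 0.8 = 25 per group, 75 in total. The 20 per group does not follow from the stated inputs alone, because the test type and the correlation between visits are not given. The point here does not depend on it; I take 20 per arm as the number analysed.

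**Assumptions.** Unit SD at each visit, equal correlation r between visits of 0.5 or 0.7, normal data, no missing visits. The article gives no correlation, so results are shown as a range over the two values.

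**Size of effect.** If only SEQ differs, by d, the SD of the three arm means is d × √2/3. Setting this to f = 0.30 gives d = 0.30 × 3/√2 = 0.636 SD.

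**Dilution in the group main effect.** With arm differences δ₀, δ₁, δ₂ at the three visits, the group term tests (δ₀ + δ₁ + δ₂)/3, and δ₀ is 0 in expectation.
- Lasting benefit: (0 + d + d)/3 = 2d/3, so 0.636 becomes 0.42.
- Post-test only: (0 + d + 0)/3 = d/3, so 0.636 becomes 0.21.

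Simulated with a lasting d = 0.5 SD in SEQ and 20 per arm, the group term is significant in 20–24% of trials and the interaction in 34–55%.

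**Baseline imbalance in the group main effect.** A chance pretest difference b is expected to persist as r × b at each later visit, so the group term picks up b(1 + 2r)/3. That is 0.67b at r = 0.5 and 0.80b at r = 0.7. If SEQ stands 0.5 SD ahead at every visit with no treatment effect, the group term is significant in 41–48% of trials (20 per arm) and the interaction in 5%. This is conditional on such an imbalance; over all randomisations the group term stays at 5%.

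**How often post hoc testing opens.** If the three tests were independent, the chance of at least one trigger with no effects would be 1 − 0.95³ = 14.3%. Simulated, 20 per arm:

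| Scenario | Time effect | Interaction | Any trigger | Any false arm difference, if Tukey compares arm means |
|---|---|---|---|---|
| No effects | 5% | 5% | 14–15% | about 5% |
| Shared gain of 0.3 SD, no arm difference | 66–88% | 5% | 69–89% | about 5% |

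**Finding a real benefit.** SEQ 0.636 SD better at post-test, 20 per arm:

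| Analysis | r = 0.5 | r = 0.7 |
|---|---|---|
| Group × time interaction (omnibus, names no pair) | 53% | 79% |
| Tukey on post-minus-pre change, a given SEQ pair | 35% | 59% |
| Baseline-adjusted post-test contrast, Tukey critical value, same pair | 46% | 65% |

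The last two rows differ because of residual variance. A change score has variance 2(1 − r), which is 1.00 at r = 0.5 and 0.60 at r = 0.7. The baseline-adjusted outcome has 1 − r², which is 0.75 and 0.51.

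**The case against.** Following up a main effect is ordinary ANOVA practice. The abstract also sets out to describe change over the three assessments, which a time effect serves. The interaction is listed first in the rule and has reasonable power. The group main effect is a valid 5% test under randomisation, so its weakness is efficiency, not bias. The Discussion acknowledges that there is no passive control. All of this stands.

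Three stronger readings are tempting but not supported.

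- **The trigger rates are false-positive rates for treatment.** They are not. A shared time trend cancels between arms, so Tukey on arm means still declares a false arm difference in only about 5% of trials.
- **Tukey's test will compare only arm means averaged over the visits, so a real benefit will usually be missed.** The article does not say which means are compared, and it does not exclude change scores or visit-specific means. The interaction would also still be reported.
- **The investigators will present a shared time trend as a benefit of training.** Nothing states this, and the Background frames the effect as SEQ against the single trainings.

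Eta-squared is unsigned and omnibus, so it cannot show which arm is better. It is offered alongside p values, however, and nobody claims that it shows direction. Keeping it does no harm.

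What remains is that the only stated route to the intervention effect does not say which term carries it.

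**Conclusion.** The point holds as a fault in a rule that the article states outright, and it is not a detail merely left to an analysis plan. The time effect cannot support a treatment claim in this design. The group effect is valid but diluted to two thirds or one third of the true difference, and it is open to chance imbalance at pretest. The rule therefore opens post hoc testing for reasons unrelated to treatment in 14–15% of trials with no effects, and in 69–89% with a shared 0.3 SD gain.

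No inflated rate of false arm differences has been shown. The gain from the change is clarity about what counts as a treatment effect, plus power to identify the pair: 46–65% with baseline adjustment against 35–59% with change scores. The dilution factors are exact. The percentages rest on the assumed correlations, the equal-correlation structure, 20 analysed per arm and the chosen effects.

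**What to change.** Replace the sentence on Tukey's test with wording to this effect: *The intervention effect is the between-arm difference adjusted for the pretest value, at post-test and at 6 months. All three pairs are reported at each visit with Tukey-adjusted comparisons and 95% confidence intervals. The group × time interaction is the omnibus test. Time and group main effects may be described, but no claim about an intervention effect rests on them.*

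The physiological markers are collected only at baseline and immediately after the programme, so only the post-test contrast applies to them. Eta-squared may stay as a supplement.

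The cost is analysis wording. The pretest is already collected, no extra patients or visits are needed, and the article lists the trial as still recruiting, so the change can be made before the data are analysed.

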### Primary outcome measure: cognitive functions

The Montreal Cognitive Assessment (MoCA) is a 30-point test that examines general cognitive functions, including memory, attention, language, visuospatial ability and execution, naming, delayed recall, abstraction, and orientation. The MoCA is a feasible tool to evaluate the global cognitive function in a large population of patients with stroke [33]. Good-to-excellent reliability and validity have been established in patients with cerebrovascular disease [34].

The Wechsler Memory Scale – Third Edition (WMS–III), a standardized and reliable neuropsychological tool, is designed to evaluate visuospatial and memory functions [35]. The Faces Recognition, Verbal Paired Associates, Word Lists, and Spatial Span WMS–III subtests will be used to assess the immediate, delayed, and working memory [36]. For the Faces Recognition test, the participant will be required to look through all of the faces and recognize those faces later. For the Verbal Paired Associates test, the participant will be instructed to memorize several pairs of words and then will be asked to respond to the appropriate word that matches the test word. In the Word Lists test, the instructor will read out a list of words, and the participants will be instructed to repeat as many words as they can immediately and 30 minutes afterwards. During the Spatial Span test, the instructor will point to spatially located blocks in a sequential order; the participants will be instructed to touch the blocks in the same sequential order or a reversed order.

The Wechsler Adult Intelligence Scale – Third Edition (WAIS–III) is a widely used and accepted assessment tool for verbal comprehension, working memory, perceptual organization, and processing speed [37], with high reliability and validity, and is often used to differentiate individuals with cognitive deficits from those with intact cognitive functions. We will use the Digit Symbol-Coding and Matrix Reasoning tests. The Digit Symbol-Coding test consists of 9 digit-symbol pairs, and the participants will be asked to write the corresponding symbols for the given digits on the test sheet as accurately and as fast as possible. The Matrix Reasoning test requires the participants to solve missing puzzles within given matrixes, which entail the abilities of visual-spatial reasoning, abstract reasoning, visual organization, and visuospatial information processing [36].

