The Useful Field of View (UFOV) is a computer-based visual test that assesses visuomotor processing speed, divided attention, and selective attention. The UFOV is the visual area over which information can be extracted from a brief glance without eye or head movements. The UFOV has good test-retest reliability and validity to assess patients with stroke [38].

The Stroop Color-Word test assesses the abilities of selective attention, inhibition, and executive function. The participants will be tested under congruent and incongruent conditions. In the congruent condition, the participant will name the color of the ink of a word, which is consistent with the written color name; whereas, in the incongruent condition, the participant will name the color of the ink, which differs from the written color name. In both conditions, the number of colors correctly named within 45 seconds will be measured, and the performance in the congruent condition will be compared with the incongruent condition.

The dual-task test evaluates the ability to shift attention between one task and another. Participants will perform the Box and Block test (BBT) while doing secondary cognitive tasks while sitting. Participants will perform the BBT using the affected and less affected hand. Two cognitive secondary tasks will be performed: (1) arithmetic task: participants will be asked to perform serial subtractions by 3 starting from 100 or random two-digit numbers (e.g., as previously described [39]); (2) tone discrimination task: participants will be presented a number of low-pitched and high-pitched tones and will calculate and remember the number of high-pitched tones during the trial. Both cognitive task performances will be recorded and the results compared against a single cognitive task performance. Participants will perform both secondary cognitive tasks while walking.

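### The primary outcome is a cognitive battery of at least ten scores with no lead score or composite, and every comparison is tested at an unadjusted 0.05, so the error rate for the primary hypothesis is not controlled

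*Protocol article*

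**What the plan says.** The relevant section of the protocol article is headed "Primary outcome measure: cognitive functions". The heading is singular, but it names a domain. Six instruments follow under it:

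- MoCA, introduced as "The Montreal Cognitive Assessment (MoCA) is a 30-point test that examines general cognitive functions".
- WMS-III, four subtests: "The Faces Recognition, Verbal Paired Associates, Word Lists, and Spatial Span WMS–III subtests will be used".
- WAIS-III, two subtests: "We will use the Digit Symbol-Coding and Matrix Reasoning tests".
- UFOV, a "computer-based visual test that assesses visuomotor processing speed, divided attention, and selective attention".
- The Stroop Color-Word test, in two conditions that are compared with each other.
- A dual-task battery: "The dual-task test evaluates the ability to shift attention between one task and another". It has two secondary tasks, uses both hands, and is repeated while walking.

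None of these is marked as the lead, and no composite or order of testing is given.

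The Analyses section prescribes a mixed repeated-measures ANOVA with three groups and three times, Tukey's test after an interaction or a main effect, and an effect size for each outcome measure. On the significance level it says: "Statistical significance will be set at 0.05 for all comparisons".

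The Sample size section uses f = 0.30, power 0.80 and one undivided two-sided alpha of 0.05. It does not tie the calculation to any named score in this trial.

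**The concern.** The Background section presents the trial as an adequately powered test of one hypothesis: that the sequential combination improves cognitive performance. With ten or more scores under the primary heading, each tested at 0.05, nothing in the article says which result would confirm or refute that hypothesis. A single significant subtest could be reported as support, and so could a different one chosen after the data are seen. The chance of such a result under no true effect is then well above the nominal 5%.

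This is more than detail left to a fuller document. The sentence on the significance level is a stated rule, and a later analysis plan that adjusted across outcomes would contradict it.

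**Working it through.** The article states no familywise error rate, so there is no figure of its own to reproduce on this point.

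**1. Number of scores** (section on the primary outcome). The minimum reading is one score per instrument or named subtest:

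MoCA 1 + WMS-III 4 + WAIS-III 2 + UFOV 1 + Stroop 1 + dual-task 1 = 10.

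The reading most favourable to the plan is one score per instrument, which gives 6.

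**2. Independent scores.** With one group × time test per score at 0.05 and no true effect, P(at least one p < 0.05) = 1 − 0.95^m.

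- m = 10: 1 − 0.95^10 = 0.401, or 0.401 / 0.05 ≈ 8 times nominal.
- m = 6: 1 − 0.95^6 = 0.265, or about 5 times nominal.

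**3. Correlated scores.** Scores from the same patients will correlate, but the article does not say how strongly. The group × time F test was simulated under the null with 20 per group, three times, and a common between-score correlation r (assumed), using 20,000 trials per cell. The within-person correlation over time was set at 0.6, also an assumption.

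| r | 10 scores | 6 scores |
|---|---|---|
| 0 (formula) | 0.40 | 0.265 |
| 0.3 | 0.36 | 0.24 |
| 0.5 | 0.30 | 0.21 |
| 0.7 | 0.23 | 0.17 |
| 0.8 | 0.18 | 0.15 |

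The lowest cell, 0.15, is 0.15 / 0.05 = 3 times nominal. The highest is about 8 times.

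**4. Main effects.** The article lets a main effect as well as the interaction trigger Tukey's test. If a group main effect also counted as a finding, ten scores would give 0.64 if independent, 0.51 at r = 0.5 and 0.33 at r = 0.8. These figures are a sensitivity check and are not used in the conclusion.

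**5. What Tukey's test covers.** It adjusts the pairwise comparisons that follow one significant ANOVA effect. It leaves steps 2 and 3 unchanged.

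**6. Power cost of a remedy.**

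- *Adjusting over ten scores.* Bonferroni gives 0.05 / 10 = 0.005 per test. The article does not name its test family. The variant that comes closest to its 20 per group is the between-group test over three measures with an assumed within-person correlation of 0.3, where power at N = 60 is 0.799. At 0.005 that falls to 0.477, and the N for 80% power rises from 63 to 99 before attrition.
- *One score, two contrasts.* Suppose f = 0.30 means that the sequential arm alone differs. Group means of 0, 0 and d give f = d√2 / 3, so d = 0.30 × 3 / √2 = 0.64. With 20 per group and 0.025 per contrast, a two-sample t-test has power of about 0.38. Adjusting for a baseline that correlates 0.5 or 0.7 with the outcome raises this to about 0.50 or 0.68.

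**The case against.** Four points can be made for the plan.

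*The success rule is inferred.* No sentence says that one significant score suffices. This stands, so the error rates above are conditional on that reading. The article offers no alternative rule, which leaves the reading open.

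*Hierarchy and multiplicity may sit in a fuller document.* An article can leave these to the full protocol or analysis plan, and the absence of a success criterion taken alone would be that kind of gap. It does not excuse a sentence that fixes 0.05 for everything, or a primary heading that covers six instruments.

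*The 40% figure needs independent scores.* That is implausible for cognitive tests in the same patients. This stands too, which is why the range is given. At r = 0.8 the figure is still 0.18 for ten scores and 0.15 for six.

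*The trial is partly exploratory.* The abstract's discussion speaks of exploring benefits. The Background section, however, claims an adequately powered hypothesis test.

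Three stronger readings are tempting, but the article does not support them:

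- A reader might infer a further chance of success at either of the two post-baseline visits. The Analyses section describes one ANOVA over all three times, not a test at each visit.
- A reader might count 15 or more scores. Only Word Lists is described as both immediate and delayed, the Stroop conditions are compared with each other, and UFOV is described by abilities rather than by analysed scores. The dual-task test may well give several scores, but the article does not fix how many. Ten is the supportable minimum.
- A reader might conclude that the sample size was computed for one test of one score. The Sample size section names neither, and its use of the lowest effect size from a study with several measures may be an attempt to cover more than one outcome. It shows only that alpha was not divided.

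**Conclusion.** The concern holds. The primary outcome is a domain with at least ten scores, no lead score or composite, and a stated unadjusted 0.05 that Tukey's test does not offset across outcomes. If any one significant group × time result may be read as support for the primary hypothesis, the false-positive chance is 0.40 for ten independent scores, about 0.30 at r = 0.5 and about 0.18 at r = 0.8. For six instruments it is about 0.15 to 0.27. That is roughly 3 to 8 times 5%.

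The size rests on two assumptions that the article does not settle: the any-one-score reading and the between-score correlation. That the error rate across the battery is uncontrolled depends on neither. The planned 20 per group is not shown to be wrong, and the point does not rely on it.

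**What to change.** Before unblinding, choose one of two routes:

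- **(a) One primary.** Name one cognitive score, or a prespecified composite of the battery, tested at an overall 0.05, and make the other cognitive scores secondary. MoCA total is a natural candidate as the only global measure. Its drawback is that MoCA below 26 is also an entry criterion, so baseline values are selected. The choice is the sponsor's.
- **(b) Co-listed primaries.** Keep the battery, list exactly which scores belong to it, and control familywise error across them, for example with Holm's procedure.

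Under either route, replace the sentence on the significance level so that unadjusted 0.05 results outside the primary test are labelled supportive.

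The trial was recruiting when the article was written, so if the data are still blinded the change is mainly one of wording in the outcome and analysis sections, with the registry entry brought into line where it differs. There is also a statistical cost. Route (a) narrows the headline claim. If 0.05 is also split over two contrasts with the sequential arm, power per contrast is about 0.38 to 0.68 under the assumptions in the working. Route (b) lowers power per score. Full Bonferroni over ten takes it from 0.799 to 0.477 in the variant shown, and Holm does no worse than that. Restate the power for the option chosen.
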